### Interim analyses {21b}

Not applicable, no interim analyses are planned.

### Methods for additional analyses (e.g., subgroup analyses) {20b}

Subgroup analyses will be specified in the statistical analysis plan and will include subgroups stratified by tumor recurrence and experience of other major diseases or life events during the course of the intervention. Sensitivity analyses of the primary endpoint will include variations in the handling of missing data. Furthermore, the primary endpoint will be evaluated in the intention-to-treat (ITT) and per-protocol (PP) populations. Further sensitivity analyses include the analysis of the secondary endpoints in the ITT and PP populations.

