### Trial design {8}

The study is designed as a prospective, multicenter, two-arm randomized-controlled trial (RCT) with two parallel groups. Randomization will be performed as cluster-randomization with a 1:1 allocation. The primary objective of this trial is to test the superiority of the intervention group compared to the control group receiving standard treatment. The primary endpoint is the improvement of patients’ and parents’ self-efficacy after two months (T1) and three months (T2) in the intervention group compared to the control group.

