#### Risk-based medical care

In the intervention group, physicianss conduct a structured risk stratification in advance. Since there was no specific risk assessment tailored to childhood and adolescence at the study’s initiation, we utilized the existing risk stratification developed for adults [17] with minor adaptations for suitability in this context. Childhood cancer survivors (CCS) are classified into three risk groups (RG) based on their individual risk of developing late effects due to cancer diagnoses and treatments. The low-risk group includes patients with surgeries only (excluding brain tumor patients), patients with acute lymphoblastic leukemia (ALL) and chemotherapy alone (without radiotherapy), and patients with retinoblastoma. The moderate-risk group comprises patients with chemotherapy (excluding ALL with chemotherapy and retinoblastoma) and patients with both chemotherapy and surgery. The high-risk group includes patients who underwent radiotherapy or allogenic stem cell transplantation. Regardless of their risk group, it is recommended that all patients in the study have at least annual, long-term follow-up appointments.

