#### Psychosocial support

Before the initiation of the study, discussions with experts in this research field were conducted to identify typical psychosocial topics that families often raise in the oncological aftercare, such as questions about the transition process, health-promoting behaviors (nutrition, physical activity), the prevention of potential morbidities, and the management of the siblings’ needs. In response, materials and flyers addressing these topics were developed in accordance with recently published PanCareSurFup recommendations [18]. The psychosocial intervention is not standardized but tailored to each patient’s needs. Typically, up to four contacts with the psychosocial team over the next two months will be offered, with the frequency determined by individual needs. These sessions can take place in the clinic or via videoconference to ensure the accessibility and a low-threshold approach.

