### Implementation {16c}

The result of the cluster-randomization was communicated to all participating pediatric university clinics in March 2023. All families within one center will receive the same intervention. To ensure commitment to the study, the cluster-randomization result was disclosed only after obtaining either a bilaterally signed collaboration agreement or a letter of intent from the participating clinics, regardless of the randomization outcome.

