## Assignment of interventions: blinding

### Who will be blinded {17a}

Given the nature of the intervention, blinding of the patients and their parents is not possible. The data analysts will be blinded during the analyses.

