## Discussion

The study aims to establish and evaluate a structured multidisciplinary long-term care approach for children and adolescents, at least five years after the end of the regular cancer treatment. This approach focuses on the early detection and treatment of potential therapy-associated long-term and/ or late effects, considering both somatic and psychosocial factors. By employing evidence-based guideline recommendations [19] and utilizing risk stratification and informative materials for a successful transition, the study aims to provide high-quality healthcare to affected individuals, addressing the gap in their care and avoiding unnecessary treatment. Regular check-ups are expected to reduce long-term morbidity by enabling early treatment of potential late effects. Families who were previously unaware of their child’s risk for late effects will be informed and guided towards structured care. For adolescents’ transitioning from pediatric to adult medicine, this program offers the opportunity to be informed early about available healthcare options, facilitating a smoother transition into adult healthcare.

Beyond the potential benefits at the individual level, there are also potential implications for health economics. Currently, the positions of psychosocial workers within long-term oncological care at pediatric university hospitals in Germany are often not part of regular budget planning. Typically, they are funded exclusively through third party donations. If this trial proves that risk-based medical treatment and additional psychosocial support lead to enhancements in self-efficacy, satisfaction with the care, HRQoL, mental health problems, and transition readiness, it could significantly contribute to the funding of sufficient and multidisciplinary positions in the long-term care of pediatric cancer survivors.

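### The named subgroups are formed by events during the intervention, so treatment effects estimated within them are open to selection bias

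*Protocol article*

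**What the plan says.** The protocol article's section on additional analyses {20b} leaves the detail to the SAP but fixes part of the content: "Subgroup analyses will be specified in the statistical analysis plan and will include subgroups" of one kind, namely "subgroups stratified by tumor recurrence and experience of other major diseases or life events during the course of the intervention". It names no baseline variable alongside them and does not mark these analyses as descriptive.

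Other sections bear on the point:

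- Trial design {8}: "Randomization will be performed as cluster-randomization with a 1:1 allocation".
- Implementation {16c}: "The result of the cluster-randomization was communicated to all participating pediatric university clinics in March 2023". Trial status gives 1 July 2023 as the start of recruitment.
- Psychosocial support, intervention arm only: "up to four contacts with the psychosocial team over the next two months will be offered".
- Discussion, on the purpose of the programme: "This approach focuses on the early detection and treatment of potential therapy-associated long-term and/ or late effects".
- Blinding {17a}: "blinding of the patients and their parents is not possible".
- Risk-based medical care: "In the intervention group, physicianss conduct a structured risk stratification in advance". The article describes no matching step for control patients.

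**The concern.** A subgroup effect can be read causally when membership is settled before treatment could influence it. A stratum formed by what happens during the intervention lacks that protection. If arm changes which families are recorded as having had an event, the intervention and control families inside one stratum are selected differently. A difference between them can then appear with no true effect, or a true effect can be hidden.

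A published statement that the programme helped families who went through a new illness or life event, or helped only those who did not, would be read as a finding about whom the programme suits. These strata cannot support that reading.

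**Working it through.** The plan states no figure on this point, so there is none to reproduce. The check sets the timing and the routes side by side, and then asks when bias follows.

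**1. Timing.** Clinics knew their arm in March 2023 and recruitment began in July 2023, so every family enters after allocation is known. The useful cut-off is therefore T0, before that family's intervention starts. Major diseases and life events during the intervention fall after T0. Recurrence is less certain: the word *other* and the shared closing phrase suggest that it too is counted during the intervention, but the phrase could attach only to the later items.

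**2. Routes from arm to recorded event.**

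- Detection: finding late effects early is a stated aim of the programme.
- Contact: up to four psychosocial contacts in two months are offered in one arm only, which gives more occasions for an event to come up.
- Reporting: families know what care they receive.

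**3. Condition for bias.** Let Y1 and Y0 be a family's outcomes under intervention and control, and E1 and E0 its event status as it would be recorded under each. In stratum e the arm difference is

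E[Y1 | E1 = e] − E[Y0 | E0 = e] = E[Y1 − Y0 | E1 = e] + { E[Y0 | E1 = e] − E[Y0 | E0 = e] }.

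The first term is a treatment effect. The bracket is selection. It vanishes if arm changes no family's recorded status, or if the families whose status changes do not shift the mean of Y0 in the stratum. The documents establish neither.

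**4. What the bracket can be.** All inputs here are assumptions; none comes from the documents. The simulation used 2,000,000 subjects, no clustering and a true effect of zero. A latent vulnerability U is standard normal. The outcome has SD 1 and correlation −0.4 with U. In control, the log-odds of a recorded event are log(0.1/0.9) + 0.8U.

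| Effect of intervention arm on recording | Recorded events, intervention / control | Difference, event stratum | Difference, no-event stratum |
|---|---|---|---|
| None | 12.3% / 12.2% | +0.006 | +0.002 |
| Doubles the odds | 20.9% / 12.3% | +0.029 | +0.024 |
| Recording no longer depends on U | 9.9% / 12.2% | +0.262 | −0.036 |
| Both | 18.1% / 12.2% | +0.259 | −0.038 |

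The first row is simulation noise around zero. The third row can be checked by hand. Intervention strata there have mean 0, and the control arm as a whole has mean 0. With the control event stratum at −0.262, the control no-event stratum must sit at 0.262 × 0.122 / 0.878 = +0.036, which gives a difference of −0.036. Exchanging the arms reverses every sign. So the direction is open, and the size depends on *which* families are recorded far more than on *how many*.

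**5. Is a baseline alternative available?** The article's three late-effects risk groups are defined by diagnosis and past treatment (chemotherapy, surgery, radiotherapy, transplantation), all settled before T0. Data management {19} has medical data collected in CentraXX, and section {11c} says study nurses in both arms were trained in that documentation. The same rule could be applied to control patients if those fields are captured; the article does not list them.

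**The case against.** The other side has real substance.

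- **Bias is conditional.** A reader might infer that these subgroup effects are certainly confounded. They are not: if arm leaves the recorded events unchanged, the strata are comparable, and merely recording more events gave only 0.02 to 0.03 SD above. The larger figures rest on assumed selective detection. This stands, and *open to bias* is the accurate wording.
- **More detection is not enough by itself.** Suppose new disease is recorded in 10% of intervention and 5% of control families, and lowers self-efficacy by 0.5 SD only once known. The event strata are then −0.5 against −0.5 and the no-event strata 0 against 0. The overall arm difference of (10% − 5%) × −0.5 = −0.025 SD is a real effect of detection. Such a case produces no spurious subgroup effect, although stratifying does hide the real one.
- **The routes are partly inference.** The Discussion speaks of therapy-associated late effects, not of recurrence or life events. The article does not say that events are recorded at psychosocial contacts. The surveys follow one schedule in both arms, and medical follow-up is done as needed in both. This weakens the routes but does not close them.
- **Recurrence may mean prior history.** Eligibility allows a relapse before T0, which would make recurrence a baseline variable. That is possible, and the text should say. The disease and life-event strata are unaffected by it.
- **The list is open.** A reader might infer that the lack of a baseline subgroup is itself an error. It is not, since the SAP may add some. Adding them would not repair the strata already fixed.
- **Stratum size.** A reader might expect the strata to be too small to use. The article gives no event rate, so this cannot be claimed.

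**Conclusion.** The point holds in limited form. The article fixes subgroup comparisons on variables settled after T0, and its own text gives plausible ways for arm to affect their detection or reporting. Treatment effects within those strata are therefore not protected by randomisation and may be biased in either direction.

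The size cannot be derived from the documents. The simulated range, from nil to about 0.26 SD against the planned standardised effect of 0.3, shows only that the bias could be negligible or could rival the target effect, depending on assumptions that the documents do not settle.

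The conclusion rests on reading the closing phrase of the subgroup sentence as covering at least major diseases and life events, which the grammar requires, and on arm having some influence on what is found or reported. The primary test and the sequential testing of secondary endpoints are not touched.

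**What to change.** In the SAP, which section {20a} describes as still being written:

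1. Do not estimate treatment effects within strata defined by events during the intervention. Report recurrence, new major disease and life events by arm, and handle them as intercurrent events in a sensitivity analysis of the whole ITT set, a population already planned in section {20b}. If the stratified tables are kept, label them as descriptive only.
2. Restrict treatment-effect subgroups to variables fixed at T0, each tested by a treatment-by-subgroup interaction. Candidates are recurrence before baseline, if that was meant, and the late-effects risk group, derived by the same rule in both arms from diagnosis and treatment history, provided CentraXX holds those fields.
3. State whether tumor recurrence means before T0 or during the intervention.

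The cost is rewording and, for the risk group, central coding of control patients. No new assessments are needed if the fields are already recorded.

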### Methods in analysis to handle protocol non-adherence and any statistical methods to handle missing data {20c}

If a participant declines study participation, the attending physician notes baseline data (age, gender, cancer diagnosis, and reason for declining participation) in a list and sends the consented baseline data to Lübeck every month. For missing values in the follow-up assessments, we will conduct multiple imputations.

### Plans to give access to the full protocol, participant-level data, and statistical code {31c}

The statistical analysis plan is available on request. Due to ethical and legal considerations and in line with the informed consent form, we cannot provide access to data at the participant level.

## Oversight and monitoring

### Composition of the coordinating center and trial steering committee {5d}

The project management of the study, headquartered in Lübeck, is responsible for supervising and tracking the study’s advancement. The team consists of physicians and psychologists and receives assistance from the Institute of Social Medicine and Epidemiology as well as the Institute of Medical Biometry and Statistics. Furthermore, the study involves active participation from multiple study centers, including Augsburg, Berlin, Bonn, Erlangen, Essen, Frankfurt, Hamburg, Kiel, Mainz, and Ulm.

### Composition of the data monitoring committee, its role and reporting structure {21a}

The intervention development and statistical analyses will be carried out by separate institutes, ensuring independent processes. The data monitoring protocol and planned statistical analyses were established prior to enrolling the first patient in the study. Additionally, the trial was registered in the German Clinical Trials Register.

### Adverse event reporting and harms {22}

While the overall risk of the intervention is considered low, it is important to acknowledge that (re-) exposure to the cancer experience during psychological counseling may cause short-term psychological stress. If this occurs, the patient and/or parent will be referred to local support services, such as outpatient psychiatric or psychotherapeutic care. Any questions, events, challenges, or similar issues that arise can be discussed with the physicians in the biweekly online meeting or at any time in between by email or telephone call with the project team. Unplanned deviations and possible solutions are documented in detail by the project team. In case of unexpected severe harm that is attributable to the intervention, the Lübeck Ethics Committee and the funding organization will be informed.

### Frequency and plans for auditing trial conduct {23}

Each participating site will implement internal quality management measures to ensure the proper conduct of the study, accurate data collection, thorough documentation, and completion of case report forms. A tailored quality management plan and report will be created to evaluate each site’s performance. Prior to enrolling participants, site research staff will undergo comprehensive training on the study protocol, following standard practices. The project team in Lübeck and Bonn will monitor the quality control and reliability of screening, baseline data collection, and follow-up. Monthly study videoconferences will be held to share the results with site research coordinators and partners. If any quality assurance issues are identified, the site principal investigators and project managers will collaborate to address them.

### Plans for communicating important protocol amendments to relevant parties (e.g., trial participants, ethical committees) {25}

Any relevant changes of the intervention and the evaluation will be submitted to the ethics committees for approval. If requested, participants will also be informed.

### Dissemination plans {31a}

We will publish the results of the AELKI study in peer-reviewed journals and present them to the scientific community. We will also inform patients via relevant journals and our own newsletter, as well as via patient representative groups. Besides, we will update the trial register. Since we did not inform the patients at the beginning of the study, we do not intend to publish the datasets analyzed during the current study because of our local data protection rules.

## Discussion

The study aims to establish and evaluate a structured multidisciplinary long-term care approach for children and adolescents, at least five years after the end of the regular cancer treatment. This approach focuses on the early detection and treatment of potential therapy-associated long-term and/ or late effects, considering both somatic and psychosocial factors. By employing evidence-based guideline recommendations [19] and utilizing risk stratification and informative materials for a successful transition, the study aims to provide high-quality healthcare to affected individuals, addressing the gap in their care and avoiding unnecessary treatment. Regular check-ups are expected to reduce long-term morbidity by enabling early treatment of potential late effects. Families who were previously unaware of their child’s risk for late effects will be informed and guided towards structured care. For adolescents’ transitioning from pediatric to adult medicine, this program offers the opportunity to be informed early about available healthcare options, facilitating a smoother transition into adult healthcare.

Beyond the potential benefits at the individual level, there are also potential implications for health economics. Currently, the positions of psychosocial workers within long-term oncological care at pediatric university hospitals in Germany are often not part of regular budget planning. Typically, they are funded exclusively through third party donations. If this trial proves that risk-based medical treatment and additional psychosocial support lead to enhancements in self-efficacy, satisfaction with the care, HRQoL, mental health problems, and transition readiness, it could significantly contribute to the funding of sufficient and multidisciplinary positions in the long-term care of pediatric cancer survivors.

## Trial status

The trial is registered on the German Clinical Trials Register (https://www.drks.de/DRKS00029269) with the registration number DRKS00029269. The current protocol is version 1.0 of 1 June 2023. The recruitment started on 1 July 2023. The approximate date of recruitment completion is 30 April 2025.

## Data Availability

Currently, the data are not accessible due to the ongoing recruitment process. The study findings will be disseminated through publication in a peer-reviewed journal and presentations at scientific conferences. There is an intention to provide access to the data for researchers upon request in justified cases. To facilitate this, a transparent protocol for granting anonymized access to the data is in the planning stages, ensuring compliance with data protection guidelines in justified instances.

## Abbreviations

RCT: Randomized-controlled trial
ITT: Intention-to-treat
PP: Per-protocol
HRQoL: Health-related quality of life
